**Figure 1 figure1:**
[figure not shown]
Flowchart illustrating recruitment process, single-group design (1 intervention group), and points of assessment (preintervention, postintervention, and 6-month follow-up surveys). M-V: Mecklenburg-Western Pomerania; NRW: North Rhine-Westphalia.

### Data Management

Participation in the study is voluntary, with participants receiving detailed information about the procedure and providing informed consent according to the Declaration of Helsinki. This consent can be withdrawn anytime without justification or repercussions. Pseudonymized data can be deleted until fully anonymized, a detail made clear in the study information.

The data are stored on password-protected servers at the University of Greifswald, secured by daily backups. Access is restricted to authorized scientific personnel for qualitative and quantitative analysis. Project management and data processing staff at the university ensure data plausibility, completeness, and accuracy. After collection, data are quickly anonymized.

Data management adheres to the German Psychological Society’s recommendations, focusing on quality assurance, knowledge optimization, and maximizing cost-benefit ratios. Cleaned, anonymized primary data, along with associated syntax commands, will be openly accessible in line with open science principles, a fact communicated to participants in the study information.

### Data Analysis

#### Statistical Methods

Quantitative analyses will vary according to the different dimensions of the RE-AIM framework [71]. The software R Studio (Posit) and SPSS (IBM Corp) will be used [95]. Multilevel logistic regressions will be conducted to evaluate the dimensions of reach, acceptance, and implementation. Here, the extent to which the following variables influence institutions’ initial interest in the program, individuals’ initial willingness to participate in the program, completeness of data, and individual engagement within the program is examined: socioeconomic status, gender, age, mode of recruitment (school, youth center, and therapeutic facility), school type, performance, well-being, life satisfaction, and mental health. The initial interest of institutions in the program is operationalized by the proportion of institutions (schools, youth centers, and therapeutic institutions) that participated in an information session. The initial willingness of individuals to participate in the program is assessed by the percentage of students who decide to participate in the program after an information session. The completeness of data is examined by the percentage of data in the preintervention, postintervention, and follow-up surveys, and individual engagement is measured by the participants’ self-assessment.

For quantitative analyses of the dimensions of reach, effectiveness, and sustainability, mixed-effect multilevel regression analysis with institutions (school, youth center, and therapeutic facility), classes, and individuals as evaluation levels and 3 measurement points (preintervention, postintervention, and follow-up) will be carried out. The multilevel structure will be assumed if the actual design effect resulting from the intraclass correlation is >2 [96]. The influence of covariants such as gender, age, and socioeconomic status will be controlled. In addition, the individual courses in the outcome variables, as described before, will be examined by using latent growth models across the 3 time points. Logistic regressions will be conducted to investigate the impact of the program on participants’ addictive or disordered social media use by comparing pre- and postintervention data.

Qualitative analyses of the recruitment process will be executed by conducting a qualitative content analysis [97] using the software MAXQDA (VERBI Software). This should provide information on the barriers to participation in the program and also identify the facilitators.

Table 3 summarizes the different dimensions of the RE-AIM framework, their operationalization, and corresponding statistical methods.

**Table 3 table3:** Dimensions of the reach, effectiveness, adoption, implementation, and maintenance (RE-AIM) framework, operationalization, and statistical methods to evaluate a social media–based life skills program (leduin).

Dimension	Operationalization	Statistical method
Reach	Dependent variables Initial interest Institutional level: number of institutions (schools, youth centers, and therapeutic facilities) contacted per federal state and positive responses Individual level: proportion of adolescents who agree to participate Qualitative process information of facilitators and carriers Independent variables from questionnaires Socioeconomic status, gender, age, mode of recruitment (school, youth center, and therapeutic facility), school type, well-being, life satisfaction, and mental health	Multilevel logistic regressions Qualitative content analysis
Effectiveness	Primary outcomes: Life skills and social media–related skills Secondary outcomes: mental health, well-being, risk behavior, school performance	Mixed-effect multilevel regression analysis with institutions (school, youth center, and therapeutic facility), classes, and individuals as evaluation levels and 3 measurement points (preintervention, postintervention, and follow-up) Latent growth models Logistic regressions
Acceptance	Dependent variables Willingness to participate: Number of information events Number of consents Individual engagement Independent variables from questionnaires Socioeconomic status, gender, age, mode of recruitment (school, youth center, and therapeutic facility), school type, well-being, life satisfaction, and mental health Qualitative process information of facilitators and carriers	Multilevel logistic regressions Qualitative content analysis
Implementation	Dependent variables Completeness of data collection in the different institutions Participation of adolescents in the program on Instagram (active and passive) Independent variables from questionnaires Socioeconomic status, gender, age, mode of recruitment (school, youth center, and therapeutic facility), school type, well-being, life satisfaction, and mental health	Multilevel logistic regressions
Maintenance	Primary outcomes: life skills and social media–related skills Secondary outcomes: mental health, well-being, risk behavior, school performance Participation of adolescents in the program on Instagram (active and passive)	Mixed-effect multilevel regression analysis with institutions (school, youth center, and therapeutic facility), classes, and individuals as evaluation levels and 3 measurement points (preintervention, postintervention, follow-up) Latent growth models Logistic regressions

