## Methods

### Overview

The objectives of the accessibility study for the leduin program, grounded in the reach, effectiveness, adoption, implementation, and maintenance (RE-AIM) framework [71], primarily focus on evaluating the first dimension of the framework—“reach”—to identify effective strategies for engaging adolescents in digital life skills interventions on social media. This includes reaching a diverse demographic of 9th and 10th graders, encouraging participation, and ensuring sustained engagement. While also considering the remaining RE-AIM aspects—effectiveness, adoption, implementation, and maintenance—the study mainly seeks to understand the characteristics and engagement levels of participating adolescents and to identify what drives active or low engagement. This understanding is critical for refining recruitment strategies and enhancing the impact of social media–based health interventions for youth.

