### Data Collection

In this study, both qualitative and quantitative data are gathered to explore the RE-AIM framework’s dimensions, involving (1) documentation by the recruitment team and (2) personal-level outcomes via questionnaires. Figure 1 illustrates the study design with the recruitment phase and points of assessment.

To assess RE-AIM’s aspects of reach, acceptance, and implementation, data will be collected on the number of schools, youth centers, and therapeutic facilities contacted per state; their response rates; information events held; and consents after the event. The recruitment team will also document institutions’ responses.

Personal level characteristics outcomes, measuring reach, effectiveness, and maintenance, are gathered through web-based questionnaires in a preintervention, postintervention, and follow-up design. Participants and institutions receive unique codes for tracking. The institutional link aims for support through teachers or youth workers and therapists and thus comprehensive data collection by conducting the entire study, including data collection, within 1 school year. Schools optionally receive supplementary teaching materials for the leduin program content.

The following constructs are collected by means of questionnaires: primary outcomes (life skills [decision-making or goal setting, problem-solving, creative and critical thinking, communication, interpersonal skills and empathy, self-confidence and self-efficacy, managing emotions, and managing stress], and social media–related skills [media-based empathy, cyberbullying, smartphone, and addictive or disordered social media use]); secondary outcomes (health status [well-being, subjective health and mental health, and life satisfaction], risk behavior [substance use], and school performance); and covariants (acceptance and feasibility of the program and sociodemographic variables). Table 2 lists the survey instruments used to measure the constructs just described, including reliability.

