### Limitations

The limitations of the described approach include potential sampling bias, as engagement levels and the willingness of schools and youth centers to participate may not represent the broader adolescent population. Schools and youth centers facing significant challenges could be unable to participate in the study due to capacity constraints. This stress could be related to having a particularly burdened student body, affecting representativeness. Moreover, while directly recruiting adolescents for a social media intervention via social media platforms might initially appear to be an effective strategy, it presents substantial challenges in the context of a scientific study. The primary issue lies in the difficulty of reliably verifying adolescents’ identities and securing parental consent in an online environment. Additionally, while data collection itself is not intended to be conducted through social media, motivating adolescents to consistently participate in data collection becomes challenging without a supervised setting. This lack of direct oversight and engagement can significantly impact the reliability and consistency of data collection. Therefore, this approach is considered unfeasible for maintaining the rigorous standards required for scientific research.

The quasi-experimental design, while useful, might not fully account for confounding variables influencing engagement and outcomes. We are launching the leduin program with a digital information event, aiming for cost-effectiveness and wide reach among adolescents from diverse regions. This event serves to arouse interest. However, it is essential to thoroughly explain the scientific study’s framework accompanying the program for informed consent. While this detailed explanation may dampen interest, it is a necessary step to ensure ethical compliance and informed participation. Consequently, we will only be able to examine the characteristics of adolescents who initially agreed to participate in the study and take part in the follow-up survey. This will limit representativeness. Since we are also dependent on the voluntary participation of the participants, dropouts are to be expected, both in the program itself and in the surveys.

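### Person-level predictors of willingness to participate, and of institutional interest, cannot be estimated because only consenting adolescents supply them

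*Protocol article*

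**What the plan says.** The study's objectives "primarily focus on evaluating the first dimension of the framework", that is, reach (Methods, Overview). For this, Statistical Methods states: "Multilevel logistic regressions will be conducted to evaluate the dimensions of reach, acceptance, and implementation". Four outcomes share one sentence and one predictor list: institutions' initial interest, individuals' willingness to join, data completeness and engagement. The sentence reads in part "initial willingness to participate in the program, completeness of data, and individual engagement within the program is examined: socioeconomic status, gender, age", and the list goes on to recruitment mode, school type, performance, well-being, life satisfaction and mental health. Individual willingness is "assessed by the percentage of students who decide to participate in the program after an information session".

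The Reach row of Table 3 gives the outcome as "Individual level: proportion of adolescents who agree to participate" and labels the predictors "Independent variables from questionnaires Socioeconomic status, gender, age, mode of recruitment", continuing with school type, well-being, life satisfaction and mental health. The Acceptance row uses the same predictors for the number of consents.

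On data sources, the Data Collection section says that personal characteristics come from the web-based surveys before and after the program and at follow-up. For the wider approached population it names institutions contacted per state, response rates, "information events held; and consents after the event", plus documentation of institutions' responses. The Reach section adds recruiters' notes on reasons for joining or declining. Limitations concedes that "we will only be able to examine the characteristics of adolescents who initially agreed to participate in the study".

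**The concern.** A logistic regression of joining versus declining needs predictor values from both groups. The article describes no questionnaire for adolescents who attend an information event and then decline, and none for adolescents in institutions that never held an event. For the person-level predictors, the regression would have joiners only.

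At stake is one specific deliverable. The Abstract promises key factors that influence participation, and the findings are meant to refine recruitment and prepare a cluster-randomized trial. As written, the plan cannot say whether socioeconomic status, gender, age, performance, well-being, life satisfaction or mental health is related to the decision to join. It also contradicts its own Limitations section, which treats the restriction only as a limit on representativeness and leaves the planned regression unchanged.

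**Working it through.** The plan gives no figure for this point. Its sample size of 128 belongs to the effectiveness comparison (it reproduces as 64 per group for a two-sided t-test with d = 0.5, α = .05, power 0.8, taking medium as d = 0.5) and plays no part here.

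**Step 1: which predictors are known for whom.**

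| Predictor | Known for joiners | Known for decliners and for institutions without an event |
|---|---|---|
| Socioeconomic status, gender, age | yes, questionnaire | no |
| Well-being, life satisfaction, mental health | yes, questionnaire | no |
| Performance (text only, not in the Reach row) | yes, questionnaire | no |
| Recruitment mode, school type | yes | yes, at institution level |

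Unavailable: 3 + 3 + 1 = 7 of 9 in the text, and 3 + 3 = 6 of 8 in the Reach row of Table 3.

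**Step 2: what the willingness model does with such data.** The Results section reports 283 adolescents who agreed to participate. Suppose all of them completed the first questionnaire (fewer would change nothing). All 283 records have outcome 1 and none has outcome 0. With slopes at zero and intercept b, the log-likelihood is

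ℓ(b) = −283 × ln(1 + e^(−b))

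| b | ℓ(b) |
|---|---|
| 2 | −35.9 |
| 5 | −1.90 |
| 10 | −0.013 |
| 20 | −0.0000006 |

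It rises towards 0 and has no finite maximum. A trial fit with 283 records and three simulated covariates ended in perfect-separation warnings and a singular matrix. Random intercepts for class or institution do not help, because the outcome is constant in every cluster. More joiners only add more ones.

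**Step 3: what is missing.** The number of decliners is not reported. Under assumed consent rates among attendees, the decliners whose covariates would be needed are:

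- 50%: 283/0.5 − 283 = 283
- 30%: 283/0.3 − 283 ≈ 660
- 10%: 283/0.1 − 283 = 2547

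**Step 4: institutional interest.** The outcome is whether a contacted institution took part in an information session. Those that did not have no consenting adolescents and so no questionnaire data. Person-level predictors, or averages of them, exist only where interest was positive, which is the same fault one level up.

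**Step 5: aggregation does not rescue it.** The mean well-being or socioeconomic status of an event's consenters is selected on the outcome, and an event without consents has no mean at all.

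**Step 6: what is unaffected.** Engagement and data completeness vary among consenters, all of whom can supply the predictors. Recruitment mode and school type are known for every approached institution.

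**The case against.** The best defense is that the article does not rest its main aim on decliners. The Overview says that the study mainly seeks to understand the characteristics and engagement of participating adolescents, and the Reach section plans to describe consenters and to find predictors of engagement. Consenters' data can do both. Reasons for declining are sought qualitatively. This stands, and it bounds the point: a reader might infer that the model for the study's main objective cannot be fitted, but the documents do not support that.

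It can also be said that one pooled sentence need not put every predictor in every model, and that the questionnaire label in Table 3 is loose, since it also covers recruitment mode and school type. This carries some weight against the wording in the text. It does not clear the Reach row, which pairs the agreement outcome directly with the person-level predictors.

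Two further inferences should be resisted. One is that attendee numbers were never recorded, because Data Collection does not list them. A percentage of students joining after a session presupposes a denominator, and a condensed article may omit such a detail. The other is that engagement results will be presented as predictors of participation. Nothing in the article says so, and Limitations says openly whose characteristics can be examined.

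That disclosure does not repair the plan, however. It leaves in place a regression that needs the missing data.

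**Conclusion.** The point holds in a limited form. The coefficients of the person-level predictors (seven of nine in the text, six of eight in the Reach row) cannot be estimated for individuals' willingness or for institutions' interest at any sample size, and planning them contradicts Limitations. The Acceptance row shares the fault for consents but not for engagement. The engagement and completeness models, and the institution-level effects of recruitment mode and school type, remain usable, so the defect is confined to the participation part of the reach analysis.

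This rests on one assumption: that no decliner questionnaire exists outside the article. None is described, and the statement in Limitations excludes one. It is not a detail left to an analysis plan, because the article itself fixes model, outcome, predictors and data source.

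**What to change.** - **Willingness:** replace the person-level regression with a binomial mixed model at event or institution level (consents out of attendees). Use only predictors known for every approached unit: recruitment mode, school type and federal state. School type has no obvious value for a youth center or therapeutic facility as an institution, so it could be combined with recruitment mode in one factor.
- **Institutional interest:** use institution-level variables known for all contacted institutions.
- **Questionnaire predictors:** keep them for the engagement and data-completeness models among consenters. Describe consenters without claiming person-level predictors of participation.
- **Text:** separate the predictor lists by outcome in Statistical Methods, and amend the Reach and Acceptance rows of Table 3 to match.
- **Fallback:** 283 adolescents had already agreed by March 2024, so attendee numbers may have to be recovered from event records. If that fails, drop the willingness model and report consents descriptively.

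The cost is rewording and possibly a search of event records. No person-level claim can be made about who declines. The reduced model will also be small: the recruitment goal of 2 + 3 + 1 = 6 classes in each of 6 states gives 36 classes, plus the youth-center and therapeutic groups, and federal state alone uses five coefficients.

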For the web-based data collection of the participants’ personal data, we use the SoSci Survey platform with which we have an order data processing agreement for the leduin study that has been reviewed by the data protection officer of the University of Greifswald. This ensures the technical and organizational measures required for data security. The provider SoSci Survey works with SSL encryption (HTTPS) of the data when filling out the questionnaire and when retrieving the collected data. A secure SSL configuration (Qualys SSL Labs) secures the transmission of the data. The servers of the University of Greifswald are used to store the data. The data are secured by daily backup and are usually stored for 90 days (3 months).

The initial data collection in the pilot study proved successful due to teacher involvement. However, transferring responsibility for the subsequent data collection to the adolescents led to significant gaps in the data. To address this in the accessibility study, we will prioritize early emphasis on the importance of data collection and ensure consistent supervision of the adolescents to mitigate missing data issues.

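### The completeness model tries to explain preintervention non-completion with answers from the preintervention survey, so consenters who skipped it leave the model and the associations can be distorted in either direction

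*Protocol article*

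**What the plan says.** Under Statistical Methods, the article assigns one model family to three dimensions: "Multilevel logistic regressions will be conducted to evaluate the dimensions of reach, acceptance, and implementation". Completeness of data is one of the dependent variables, defined thus: "The completeness of data is examined by the percentage of data in the preintervention, postintervention, and follow-up surveys". The predictors are "socioeconomic status, gender, age, mode of recruitment (school, youth center, and therapeutic facility), school type, performance, well-being, life satisfaction, and mental health".

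Table 3 repeats this in the Implementation row, where the outcome, its companion outcome and the source of the predictors stand together: "Completeness of data collection in the different institutions Participation of adolescents in the program on Instagram (active and passive) Independent variables from questionnaires".

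Data Collection says how the personal characteristics are obtained. They "are gathered through web-based questionnaires in a preintervention, postintervention, and follow-up design". It also says "Participants and institutions receive unique codes for tracking", and that the recruitment team records contacts, information events and consents.

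**The concern.** The outcome counts whether the preintervention survey was filled in, and most of the predictors exist only if it was. A consenter without that survey has the worst score on this part of the outcome and no baseline value for well-being, life satisfaction, mental health or socioeconomic status. A model containing those predictors cannot use that person. Among those who remain, whole-survey non-completion at preintervention is zero by construction.

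This matters because the Implementation section presents the effectiveness of data collection as something a larger trial needs to know, and Data Collection reports that handing later surveys to the adolescents in the pilot "led to significant gaps in the data". A model meant to show who produces gaps should not lose, by its construction, those with no first survey.

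**Working it through.** **Plan's own figure.** The article gives no completeness or missingness rate, so there is none to reproduce on this point. The only related number is the 283 adolescents who had agreed to participate (Results). All rates below are assumptions.

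**Step 1: which predictors survive without a preintervention survey.**
- Known from codes and recruitment records: institution, federal state, mode of recruitment, and school type where recorded.
- Known only from a survey, as far as the article describes: socioeconomic status, well-being, life satisfaction, mental health.

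Multiple imputation does not repair this by itself. No preintervention non-responder has a baseline value, so the link between, say, baseline distress and preintervention completion rests on outside assumptions. Answers from later waves exist for only some of these adolescents and, for well-being or mental health, are measured after the program.

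**Step 2: how much missingness the regression sample hides.** Let m be the share of consenters with no preintervention survey, q the share of preintervention completers missing each later wave, and r the same share among preintervention non-completers.
- All consenters: share of survey slots missing = [m + (1 − m)·2q + m·2r] / 3.
- Regression sample: 2q / 3.

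With q = 0.30 the regression sample shows 0.60 / 3 = 20.0%. For m = 0.10 and r = 0.30, all consenters give (0.10 + 0.54 + 0.06) / 3 = 23.3%; with r = 1 they give (0.10 + 0.54 + 0.20) / 3 = 28.0%.

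| m | dropped of 283 | all consenters (r = 0.30 to 1) | regression sample |
|---|---|---|---|
| 5% | 14 | 21.7% to 24.0% | 20.0% |
| 10% | 28 | 23.3% to 28.0% | 20.0% |
| 20% | 57 | 26.7% to 36.0% | 20.0% |
| 30% | 85 | 30.0% to 44.0% | 20.0% |

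**Step 3: effect on an association.** Simulation with three logistic completion indicators per person, each survey either completed or not, sharing a person effect (SD 1.5 on the logit), and one questionnaire predictor with a log-odds effect of −0.5 per SD on completion. Later-wave completion is 67% and 59%; preintervention completion is set to 78% or 95%. The entry is the slope in preintervention completers divided by the slope in all consenters. The article names logistic regression but does not say how a percentage enters it, so two logistic versions are shown, with a linear slope for comparison.

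| Where the predictor acts | Preintervention completion | Linear slope of mean completeness | Logistic, share of three surveys | Logistic, all three complete |
|---|---|---|---|---|
| Every wave | 78% | 0.55 | 0.74 | 0.81 |
| Every wave | 95% | 0.83 | 0.89 | 0.94 to 0.95 |
| Later waves only | 78% | 0.96 | 1.30 | 1.26 |
| Later waves only | 95% | 1.00 | 1.08 | 1.05 |

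Mean completeness in the every-wave case is 68% in all consenters against 80% in the regression sample at 78% preintervention completion, and 73.7% against 76.5% at 95%.

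**Step 4: a second simulation with different settings** (about 20% preintervention non-completion, effect of 0.7 per SD on missing a survey). The odds ratio for any missing survey moves as follows from all consenters to the regression sample:
- Same effect at every wave: 2.49 to 2.28 with no person effect, 1.98 to 1.80 with a moderate one, 1.59 to 1.45 with a strong one. On the log scale, about 90%, 86% and 80% is kept.
- Effect only at later waves: 1.72 to 1.96.
- Opposite sign at preintervention: 1.54 to 2.03.
- Effect mainly at preintervention (1.2 there, 0.4 later): 1.75 to 1.31.

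With no person effect and the postintervention survey alone as the outcome, there is no bias (2.00 against 2.00). That is the case for separating the waves.

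**The case against.** **The dropped group may be small.** Data Collection says initial collection in the pilot succeeded because teachers were involved, and that the gaps came in later collection, where baseline predictors are on file. Supervision is planned again. This stands, and it is why the 95% rows are shown beside the 78% rows. It is not decisive: the pilot's success is credited to teachers, while this study also recruits through youth centers and therapeutic facilities.

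**Completeness need not be understated.** A reader might infer that the reported completeness will be too high. The documents do not support that. Consents are counted and codes assigned, so the percentage can be taken over all consenters. Table 3 words the outcome as "Completeness of data collection in the different institutions", and a percentage per institution loses nobody. Only the regression sample is affected.

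**Drivers need not be understated.** A reader might also infer that effects will always be too weak, perhaps by about half. Steps 3 and 4 show no fixed direction, and the 0.55 ratio belongs to a linear slope at an assumed 78% completion, not to the logistic model named in the article.

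**Missing-covariate handling may sit in a fuller plan.** True, and its absence from an article is not the point here. The stated pairing of outcome and predictors is, because no standard treatment of missing covariates identifies the effect of an unmeasured baseline answer on whether that baseline survey was completed.

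**The authors concede something close.** Limitations says characteristics can be examined only in those who agreed and took part in the survey. It draws the consequence for representativeness, not for this model.

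**Conclusion.** The point holds as a fault in how one outcome is paired with its predictors. Whenever some consenters lack a preintervention survey, questionnaire predictors cannot explain that non-completion, and the remaining associations describe only those who answered once. They are attenuated if the same factors act at every wave and overstated if they act only later. Under the Step 3 assumptions the logistic slope is off by roughly 20% to 30% at 78% preintervention completion, and by about 5% to 11% at 95%.

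The true size cannot be had from the article, because it states no preintervention completion rate. The conclusion assumes that the questionnaire predictors are baseline values and that people without them do not enter the model. This is a modest defect in one implementation analysis. It does not touch the effectiveness models or the raw completeness figures when these are taken over all consenters.

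**What to change.** Amend the completeness wording under Statistical Methods and in the Implementation row of Table 3:

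1. Model completion of the preintervention survey in all consenters, using only variables known from codes and recruitment records: mode of recruitment, institution, state, and school type where recorded.
2. Model completion of the postintervention and follow-up surveys in preintervention responders, using their baseline questionnaire answers, and state that these results are conditional on preintervention response.
3. Report completeness for each wave with all consenters as the denominator.

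No new data are needed. The cost is two models in place of one, and an open statement that the effects of questionnaire predictors on preintervention non-completion are not estimable in this study.
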